### Statistics

***Sample size calculation***. We assume the viral clearance time from throat/nose swabs to have a log-normal distribution. Using data from 14 patients in Ho Chi Minh City and Singapore, we estimated the mean time to clearance (natural log scale) of 2.17 days and standard deviation 0.74 ([name] [name], personal communication, 13 February 2020 and [name] [name], personal communication, 12 February 2020). 120 patients will give 80% power to detect a reduction in the time to viral clearance by at least a factor 0.68. If the trial completes enrolment and is not stopped early due to safety, efficacy or futility, we will enrol 240 patients. A sample size of 240 patients will give 80% power to detect a reduction in the time to viral clearance by at least a factor 0.76.

***Statistical and analytical plans***. Study analysis will be according to an
*a priori* defined statistical analysis plan, which will be completed before database locking. The primary endpoint is virological and robust and will be performed by technicians unaware of the treatment allocation of the patient. In that sense the study therefore is blinded. The time to viral clearance will be defined as the time from randomization to the midpoint between the last positive and the first of at least two consecutive daily negative viral PCR tests on throat/nose swab. Data will be illustrated with time to event curves and analysed using the log rank test and Cox model.

***Secondary endpoints***.

Survival until 56 days after randomization

Overall survival will be visualized using Kaplan-Meier curves and modelled using the Cox proportional hazards regression model with stratification by disease severity. In addition, survival will be modelled with a multivariable Cox regression model including the following covariates in addition to the treatment group: age, comorbid conditions (hypertension, cardiac disease, diabetes, ACEA inhibitor or angiotensin receptor blocker use).

AEs

The frequency of serious and grade 3 and 4 ARs as well as the frequency of specific AEs will be summarized (both in terms of the total number of events as well as the number of participants with at least one event). The proportion of participants with at least one such event (overall and for each specific event separately) will be summarized and (informally) compared between the two treatment groups based on Fisher’s exact test if the expected number in one of the cells is at most one and the chi-square test if expected number in each cell is larger than one.

Analysis of other secondary outcomes

1. The duration of hospital stay from the time of randomization.2. The number of ventilator-free days during the first 28 days following randomization.3. The time to (all-cause) death following the first 10, 28, and 56 days since randomization.4. The WHO ordinal outcome scale for COVID-19 at days 28, 42 and 56
^24^.5. Fever clearance time.6. Development of ARDS defined by the Kigali criteria
^25^.7. Oxygenation-free days over the first 28 days.

The analyses of these secondary endpoints will be defined in the statistical analysis plan.

***Statistical hypotheses***. The primary null hypothesis is that the rate of clearance of virus from throat/nose swabs is not different between chloroquine compared with standard of care therapy.

***Analysis datasets***. The primary analysis population for all analysis is the full analysis population containing all randomized participants except for those mistakenly randomized without COVID-19. Participants will be analysed according to their randomized arm (intention-to-treat). In addition, the primary endpoint will be analysed on the per-protocol population, which will exclude the following participants: major protocol violations and those receiving less than one week of administration of chloroquine for reasons other than death.

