***Randomization and treatment allocation***. Randomization will be 1:1 to either chloroquine or standard of care treatment. Randomization with variable block sizes of four and six will be used to assign subjects to treatment. Randomization will be stratified by recruiting centre and disease severity. The randomization list will be generated according to the OUCRU randomization and drug dispensing SOP. In brief, the study statistician will set up statistical code to generate the randomization list and transfer it to the central study pharmacist. The study pharmacist will change the random seed, i.e. the initialization of the random numbers generator, in the statistical code in order to blind the study statistician and then run the code to prepare the final randomization list for treatment preparation. The randomization list will be password protected and stored on a secure server to which only the study pharmacist has access. Based on the randomization list, the study pharmacist will prepare randomization envelopes and generate identical sealed treatment packs for each study ID and distribute them to the sites in batches as required. Each pack will contain sufficient chloroquine for the 10 days of treatment. Enrolment logs specific to each study site will be used to assign participants to the next available sequential number and corresponding sealed treatment pack.

***Study intervention***. Chloroquine will be administered orally, as tablets. For unconscious participants chloroquine can be crushed and administered as a suspension via a nasogastric tube. A loading dose, administered with food where possible, is given on the first study day. Following the first 24 hours, participants will receive a dose of chloroquine phosphate salt of 500mg once daily until 10 days after randomization (unless they are <53kg, when the dose will be reduced, see
Table 2).

Chloroquine has complex pharmacokinetic properties with an enormous apparent volume of distribution (200–300 L/kg) and a terminal elimination half-life of 1–2 months, so concentrations in plasma (and rapidly exchanging tissue compartments) are determined predominantly by distribution not elimination. Given that EC50 values against the SARS-CoV-2 virus are in the low micromolar range
*in vitro*, which suggests moderate activity, it is likely that relatively high concentrations will be required for maximum effects

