If a participant chooses to discontinue their trial treatment (chloroquine), they should always be followed up (providing they are willing) and they should be encouraged not to leave the whole trial. If they do not wish to remain in trial follow-up, however, their decision must be respected and the participant will be withdrawn from the trial. The reason for the participant withdrawing should be ascertained wherever possible. Prior to withdrawing from the trial, the participant will be asked to have assessments performed as appropriate for the final visit although they would be at liberty to refuse any or all components of the assessment.

If a participant withdraws from the trial, the medical data collected during their previous consented participation in the trial will be kept and used in analysis. Consent for future use of stored samples already collected can be refused when leaving the trial early (but this should be discouraged and should follow a discussion). If consent for future use of stored samples already collected is refused, then all such samples will be destroyed following the policies of the institution where the samples reside at the time (local or central storage). Participants may change their minds about stopping trial follow-up at any time and re-consent to participation in the trial. Participants who stop trial follow-up early will not be replaced, as the total sample size includes adjustment for losses to follow-up.

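### The stated 80% power matches a comparison of mean log clearance times; under the same log-normal planning model the named log-rank/Cox analysis has about 73-74%

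*Protocol article*

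**What the plan says.** All the main elements stand in the Statistics section of the protocol article.

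- Planning model (Sample size calculation): "We assume the viral clearance time from throat/nose swabs to have a log-normal distribution". From 14 patients, "we estimated the mean time to clearance (natural log scale) of 2.17 days and standard deviation 0.74".
- Power claim for the smaller size (same paragraph): "120 patients will give 80% power to detect a reduction in the time to viral clearance by at least a factor 0.68".
- Power claim for the full size (same paragraph): "A sample size of 240 patients will give 80% power to detect a reduction in the time to viral clearance"; here the stated factor is 0.76. No test, significance level or sidedness is given for either figure.
- Analysis of the primary endpoint (Statistical and analytical plans): "Data will be illustrated with time to event curves and analysed using the log rank test and Cox model".
- Allocation (Study procedures): "Randomization will be 1:1 to either chloroquine or standard of care treatment".
- Losses (Study procedures, on discontinuation): "the total sample size includes adjustment for losses to follow-up". No rate is given.

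The article plans no comparison of mean log times and no log-normal regression.

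**The concern.** The power statement and the named analysis sit in adjacent paragraphs and concern the same endpoint, so a reader takes the 80% to be the power of the log-rank test and Cox model. The sizing effect, however, is a multiplicative shift of a log-normal time. Such a shift does not give proportional hazards: the hazard ratio for clearance is largest early and then falls towards 1. The log-rank test and Cox model are most efficient under proportional hazards and lose efficiency here. If the 80% came from a comparison of log means, the analysis that will be run has less power than stated under the plan's own assumptions.

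At stake is the type II error on the primary endpoint (about 26% rather than 20%) and how a null result would be read. The 120-patient figure also coincides with the interim look at which futility is to be assessed. There is a smaller question of scale: the design target is a time ratio, while a Cox model reports a hazard ratio.

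**Working it through.** **Inputs.** From the document: log-normal times, log-scale mean 2.17, SD 0.74, 1:1 allocation, N = 120 with factor 0.68, N = 240 with factor 0.76. Assumed: two-sided 5% and no losses.

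**1. Reproduce the stated 80%.** For a comparison of mean log times, power = Φ(|ln f| / (SD × √(4/N)) − 1.96).

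- N = 120, f = 0.68: |ln f| = 0.3857; SE = 0.74 × √(4/120) = 0.1351; ratio 2.855; power 81.4% (t-test 80.8%).
- N = 240, f = 0.76: |ln f| = 0.2744; SE = 0.74 × √(4/240) = 0.0955; ratio 2.873; power 81.9% (t-test 81.6%).
- Factor at exactly 80%: exp(−2.802 × SE) = 0.685 and 0.765, in line with the stated 0.68 and 0.76.

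Other readings do not fit. One-sided 5% gives 89% at both sizes. Treating the factor as a hazard ratio with every patient an event (Schoenfeld) gives 56-57%.

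**2. Log-rank power under the same model, analytically.** For a normal shift on the log scale, the asymptotic efficiency of the log-rank (Savage) scores relative to the comparison of means is 0.816 by numerical integration. The ratio in step 1 is therefore multiplied by √0.816 = 0.903.

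- N = 120: 2.855 × 0.903 = 2.578; Φ(2.578 − 1.96) = 73.2%.
- N = 240: 2.873 × 0.903 = 2.595; Φ(2.595 − 1.96) = 73.7%.

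**3. Log-rank power by simulation** (20,000 trials per scenario).

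| N, factor | No censoring, continuous times | Range over daily rounding and censoring at day 14, 21, 28 or 56 |
|---|---|---|
| 120, 0.68 | 73.6% | 73.2-73.9% |
| 240, 0.76 | 74.0% | 73.7-74.9% |

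A second run with another seed gave 73.1% and 73.5% (continuous times, no censoring). The Cox Wald test (2,000 trials, simulation error about 1 point) gave 75% and 72%. Swab timing and censoring do not drive the result.

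**4. What would give 80% with the log-rank test.**

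- Factor: exp(−2.802 × SE / 0.903) = 0.658 (N = 120) and 0.744 (N = 240). At the rounded values 0.66 and 0.745, simulated power is 79%, so these are 80% to rounding.
- Sample size at 0.76: the log-mean formula needs 228.3 patients in total (115 per arm, 230). Dividing by the efficiency, 228.3 / 0.816 ≈ 280. Simulation at 280 gives 80.5%.

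**5. Effect scale.** For factor 0.76 under the planning model, the hazard ratio for clearance is about 2.0 at day 2, 1.33 at day 8 and 1.16 at day 28. The average Cox hazard ratio was about 1.40, and about 1.64 for factor 0.68. A single Cox estimate therefore does not translate directly into the design factor.

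**6. Losses.** The log-mean calculation needs 230 of the 240 patients, which leaves 10 (about 4%) for losses. Any losses would lower the figures in steps 2 and 3.

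**The case against.** The strongest reply concedes the arithmetic and contests its weight.

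- *The gap depends on the distribution.* With the same log-scale SD and time ratios but Weibull times, where hazards are proportional, simulated log-rank power is about 95% at both sizes, against 81-82% for the t-test on log time. With log-logistic times it is about 74%. Fourteen patients cannot settle the shape. This stands: the shortfall belongs to the planning model and is not a known property of the trial.
- *The planning SD is far more uncertain than the gap.* A chi-square 95% interval for an SD of 0.74 from 14 patients is about 0.54 to 1.19. Over that range the log-mean comparison at 0.76 and N = 240 runs from about 98% to 43% power. This also stands, and it limits the practical weight of 6 points. It does not make the stated figure right for the stated inputs.
- *Nothing is invalid.* The log-rank test keeps its type I error when hazards are not proportional. The protocol's primary null hypothesis concerns the rate of clearance, which suits a log-rank or Cox analysis. Both points stand.
- *The test behind the 80% is inferred.* True: the article names no test or significance level. But one standard calculation reproduces both figures and the alternatives tried do not.

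A reader might go further and infer that the primary analysis is wrong and must be replaced by a log-normal model. The documents do not support that. Such a model would tie the confirmatory test to a shape backed by 14 patients, and in the Weibull case a comparison of log means loses about 14 points of power against the log-rank test.

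**Conclusion.** The point holds in a limited form. Under the protocol's own planning model, and assuming two-sided 5% and no losses, the 80% figures match a comparison of mean log clearance times. The named log-rank/Cox analysis has about 73-74% power at 0.68 with 120 patients and at 0.76 with 240. The shortfall is about 6 points against the stated 80% and 7-8 against the log-mean comparison.

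The power statement is therefore wrong for the analysis named beside it, and nothing elsewhere in the article repairs it. A reader might also infer that the trial is underpowered in fact. That does not follow: the shortfall is conditional on log-normality, and another plausible shape reverses it. The planned test remains valid.

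**What to change.** In the Sample size calculation paragraph:

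1. Restate the power for the log-rank test under the log-normal model. Either give about 73-74% at factors 0.68 (120 patients) and 0.76 (240 patients), or give 80% at about 0.66 and 0.745.
2. Name the test, significance level and sidedness behind the figures, and the loss rate that the sample size is said to allow for.

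Optionally, prespecify a log-normal accelerated failure time model as a supporting analysis that reports the time ratio with a 95% confidence interval. The result could then be read on the scale used for sizing. Making that model primary would recover the power if log-normality holds, at the price of relying on that shape. It is a choice for the sponsor.

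The cost is wording in the protocol and the analysis plan, with no extra patients or data, and a less favourable power statement. The article reports two participants enrolled and says the analysis plan will be completed before database lock, so the change can be made prospectively.

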### Study design

The study will start with a 10-patient prospective observational pilot study following the same entry and exclusion criteria as for the randomized trial and undergoing the same procedures. All 10 participants will receive chloroquine at the doses used in the trial; they will not be randomized. The purpose of the pilot study is to develop the study procedures for the randomized controlled trial, including the safe monitoring of participants, and to acquire some preliminary data on the safety of chloroquine in those with COVID-19 in Vietnam. Data from these patients will not be included in the final analysis. Once the pilot study has been completed, and the data reviewed by the trial steering committee (TSC), the data monitoring committee (DMC), and the Ministry of Health (MoH) ethics committee (EC), we will proceed with the trial. We aim for minimum delay between completing the pilot study and starting the randomized trial.

The main study is an open label, randomised, controlled trial with two parallel arms of standard of care (control arm) versus standard of care with 10 days of chloroquine (intervention arm) with a loading dose over the first 24 hours, followed by 300mg base orally once daily for nine days. The study will recruit patients in three sites in Ho Chi Minh City, Vietnam: the Hospital for Tropical Diseases (HTD), the Cu Chi Field Hospital, and the Can Gio COVID hospital. Additional sites including the National Hospital for Tropical Diseases in Ha Noi, Vietnam will be added based on enrolment rates.

All adult patients (≥18 years old) presenting to the study centres with positive throat/nose swabs (RT-PCR) for SARS-CoV-2 and requiring hospital admission will be eligible for study inclusion subject to the inclusion and exclusion criteria. Randomization will be stratified by severity of illness with severe disease being defined by a SpO2 ≤94%, or tachypnea (respiratory rate ≥24 breaths/min), and mild-moderate disease being defined by SpO2 >94% and respiratory rate <24 breaths/min without supplemental oxygen.

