*in vivo*. The intervention dose was chosen following evidence review and discussion with healthcare partners. We aimed for an initial loading dose of 10mg/kg base, followed by 5mg/kg base at 6 hours and every 24 hours until 10 days after randomization. The (maximum) dosage used for an adult ≥53 kg is as shown in
Table 2.

**Table 2. T2:** A) Maximum chloroquine dose for an adult ≥53 kg enrolled in the VICO trial. B) Maximum chloroquine dose for an adult <53 kg enrolled in the VICO trial.

**A**			
		Total chloroquine (CQ) dose	
Time	Number of tablets	Chloroquine base	Chloroquine phosphate
Initial dose T=0	4	600mg	1000mg
T=6 hours	2	300mg	500mg
Thereafter	2 once daily for 9 days	300mg once daily	500mg once daily
**B**			
	For an adult 52-45 kg	For an adult <45-38 kg	For an adult <38 kg
Time	Number of tablets	Number of tablets	Number of tablets
Initial dose T=0	3.5	3	2.5
T=6 hours	2	1.5	1.5
Thereafter	2 once daily for 9 days	1.5 once daily for 9 days	1.5 once daily for 9 days

Patients with severe renal impairment or elevated blood transaminases are excluded from the study (see inclusion and exclusion criteria). If an enrolled patient develops cardiac arrhythmia or syncope, chloroquine will be stopped and an electrocardiogram (ECG) performed. Electrolytes (Na, K, Ca, Mg) will be checked and corrected as necessary. Where significant asymptomatic QTc prolongation is identified (>500ms), chloroquine administration will be interrupted, electrolytes checked and corrected, and the drug reintroduced when the QTc is <480ms. Particular care will be taken in those who take other medications, which may prolong QTc.

***Baseline assessment***.

Clinical assessment: All participants will have a full clinical assessment including medical history and examination by the study team. Data collected will include presenting symptoms, duration of illness, past medical history, current medications, and physical examination findings including vital signs (pulse, temperature, blood pressure, oxygen saturations and FiO2), and the results of cardiovascular, respiratory, gastrointestinal and neurological examination in line with standard clinical practice.

Radiology: The results of any radiological imaging (chest X-ray, computed tomography (CT) scan, lung ultrasound) performed during the participant’s illness will be recorded in the clinical reporting form. Participants who have not had a chest X-ray will undergo a chest X-ray on study entry.

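### The primary log-rank test and Cox model are stated without the centre and severity strata used at randomisation; run that way, the test is conservative and can lose power

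*Protocol article*

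**What the plan says.** All references are to the protocol article.

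- **Randomisation** (Study procedures, Randomization and treatment allocation): the two arms are allocated in equal numbers, in blocks whose size varies between 4 and 6. On the strata the section says: "Randomization will be stratified by recruiting centre and disease severity". Three named sites and two severity levels give up to six strata, and the Study design section allows sites to be added.
- **Primary analysis** (Statistics, Statistical and analytical plans): "Data will be illustrated with time to event curves and analysed using the log rank test and Cox model". No strata or covariates are named.
- **Secondary survival analysis** (Statistics, Secondary endpoints): survival is "modelled using the Cox proportional hazards regression model with stratification by disease severity", followed by a multivariable Cox model with listed covariates.
- **Deferral**: the analysis follows an a priori "defined statistical analysis plan, which will be completed before database locking". That plan is not shown. The analyses of the other secondary endpoints are expressly left to it, whereas the primary method is given in the protocol itself.

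**The concern.** Stratified randomisation balances the arms on severity and centre. If those factors predict time to clearance, the balance makes the treatment estimate less variable than it would be under simple randomisation. An ordinary log-rank test or Cox model does not know this: its standard error is computed as if the strata had been ignored at randomisation. The test then rejects less often than its nominal level under the null and less often than it could under a real effect.

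The protocol puts the severity stratum into a secondary model but does not mention it for the endpoint on which the trial is powered. What is at stake is power that could be had without another patient.

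**Working it through.** **1. The stated power.** Inputs from the sample size paragraph: SD of log clearance time 0.74; factors 0.68 (120 patients) and 0.76 (240 patients); 1:1 allocation. Two-sided alpha of 0.05 is assumed, since that paragraph does not state it.

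Power = Φ(|ln factor| / (SD × √(4/N)) − 1.96)

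- N = 240: |ln 0.76| = 0.2744; SE = 0.74 × √(4/240) = 0.0955; power 81.9%.
- N = 120: |ln 0.68| = 0.3857; SE = 0.74 × √(4/120) = 0.1351; power 81.4%.

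The stated 80% therefore reproduces for a comparison of mean log times. The log-rank test on the same log-normal data reaches about 74% at N = 240 even when the strata predict nothing (step 2, first row). That gap comes from the choice of test. It is a separate matter and is not counted here.

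**2. Unstratified against stratified log-rank.** Simulation of 4,000 trials per cell, N = 240, log-normal times with total SD 0.74, permuted blocks of 4 and 6 within 3 centres × 2 severity levels, no censoring. Assumptions not in the documents: 20% severe; centre shares 50/30/20%; three quarters of the explained variance due to severity and one quarter to centre. R² is the share of log-time variance explained by the strata. Power is at factor 0.76; type I error is at factor 1.

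| R² | Power, unstratified | Power, centre × severity | Gain (points) | Type I, unstratified | Type I, centre × severity |
|---|---|---|---|---|---|
| 0 | 73.6% | 73.2% | about 0 | 5.0% | 5.1% |
| 0.05 | 73.9% | 75.1% | 1 | 4.3% | 4.6% |
| 0.10 | 74.0% | 78.1% | 4 | 4.4% | 5.0% |
| 0.20 | 74.0% | 81.5% | 8 | 2.8% | 4.5% |
| 0.30 | 72.9% | 86.1% | 13 | 1.7% | 5.2% |

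The Monte Carlo standard error is √(0.74 × 0.26/4000) = 0.7 points for one power figure and √(0.05 × 0.95/4000) = 0.3 points for one type I figure. The R² = 0.05 row is thus barely distinguishable from no loss.

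**3. What those R² values require.** With 20% severe and severity carrying 0.75 R², the log-scale shift for severe patients is 0.74 × √(0.75 R²) / √(0.2 × 0.8). This gives 0.36, 0.51, 0.72 and 0.88 for R² = 0.05, 0.10, 0.20 and 0.30. Severe patients would take 1.4, 1.7, 2.0 and 2.4 times as long to clear.

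**4. Severity as the only stratum.** A second simulation, again at N = 240 and factor 0.76, used severity alone. R² = p(1−p)d²/0.74², with p the severe fraction and d the log-scale shift.

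| p | d | R² | Power, unstratified | Power, stratified |
|---|---|---|---|---|
| 20% | 0.4 | 0.05 | 75% | 77% |
| 20% | 0.6 | 0.11 | 74% | 78% |
| 30% | 0.6 | 0.14 | 74% | 79% |
| 30% | 0.8 | 0.25 | 75% | 85% |

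The type I error of the unstratified test was 2.7 to 4.2%.

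**5. Where the gain comes from.** First simulation, R² = 0.20:

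- Under the null, the unstratified Cox model reports a standard error of 0.130, while the estimate's actual SD is 0.116. That mismatch makes the test conservative.
- At factor 0.76 the mean log hazard ratio and model SE are 0.332 and 0.131 unstratified, against 0.387 and 0.136 stratified. The ratios are 0.332/0.131 = 2.53 and 0.387/0.136 = 2.85.
- The stratified standard error is slightly larger, so its interval is not narrower. The ratio rises because the effect within strata is larger.

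**The case against.** The strongest objection is that the protocol never says the primary analysis is unstratified. It names a family of methods immediately after committing to an analysis plan, and whether those methods carry strata is commonly settled there. This stands against a reader who infers that the sponsor has decided on an unstratified, unadjusted analysis. It does not remove the point. The protocol fixes the primary method in its own text, states stratification where it wants it for survival, and defers other endpoints explicitly. Anyone following the primary sentence as written would leave the strata out.

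Four further inferences are tempting, and the documents do not support them.

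- *The unstratified intervals are too wide.* The model standard error does overstate the estimate's real variability, but the stratified interval is no narrower. The smaller marginal hazard ratio is a different quantity from the conditional one, not an error.
- *The sections disagree on the strata.* The Study design section says "Randomization will be stratified by severity of illness with severe disease being defined by a SpO2 ≤94", going on to define the severity levels. It does not say that severity is the only factor, so it does not contradict the later section that adds centre.
- *Illness duration must be a covariate.* It is recorded at baseline ("Data collected will include presenting symptoms, duration of illness, past medical history"), but the documents give no figure for how well it predicts clearance, and recording a variable creates no duty to adjust for it.
- *The trial risks a false positive.* The error is in the safe direction.

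It is also fair to object that the size of the loss rests wholly on assumed prognostic strength. That stands, and the loss can only be given as a range.

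**Conclusion.** The point holds as an improvement to the stated primary analysis, not as a demonstrated error in the trial's conclusions. Run as written, the analysis ignores factors built into the randomisation. At 240 patients and a factor of 0.76, this costs about 1 to 13 points of power if severity and centre together explain 5 to 30% of log-time variance, and nothing if they explain none. The upper end needs severe patients to take more than twice as long to clear.

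The range assumes log-normal times with SD 0.74, a constant shift on the log scale, no censoring, two-sided alpha of 0.05, and the severe fraction and centre shares listed above. The direction follows from the design; the size is unknown until the prognostic strength of the strata is known. If the analysis plan already carries the strata into the primary analysis, only the protocol wording needs to catch up.

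**What to change.** In Statistical and analytical plans, and identically in the analysis plan, state that the primary log-rank test and Cox model are stratified by disease severity as recorded at randomisation, with centre accounted for where counts allow. Add a short rule for small or late-added sites, so that sparse centre-by-severity cells are handled in a prespecified way.

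Severity alone recovers most of the gain in the first simulation: 80.6% against 81.5% with both factors at R² = 0.20. This partly reflects the assumption that severity carries three quarters of the explained variance.

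The cost is a sentence or two. Both factors are already known at randomisation, so no data or patients are added. If the strata predict nothing, the price in power is negligible (73.2% against 73.6%). The reported hazard ratio should be described as conditional on the strata.

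### The primary log-rank test and Cox model are stated without the centre and severity strata used in randomisation, which would cost power if those strata predict clearance time

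*Protocol article*

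**What the plan says.** - **Randomisation.** Under Study procedures (Randomization and treatment allocation): "Randomization will be stratified by recruiting centre and disease severity". Allocation is 1:1, and "Randomization with variable block sizes of four and six will be used to assign subjects to treatment". The Study design section mentions severity only and defines severe and mild-moderate disease. Three centres are named and more may be added.
- **Primary analysis.** Under Statistics (Statistical and analytical plans), for time to viral clearance: "Data will be illustrated with time to event curves and analysed using the log rank test and Cox model". No stratum or covariate is named.
- **Survival.** The next paragraph has overall survival "modelled using the Cox proportional hazards regression model with stratification by disease severity", then a multivariable Cox model with listed covariates. Centre is not mentioned.
- **Other analyses.** Adverse events are compared informally by Fisher's exact or chi-square tests without strata. Analysis of the other listed secondary endpoints is left to the statistical analysis plan (SAP).
- **SAP.** Analysis follows an a priori "defined statistical analysis plan, which will be completed before database locking". It is not shown.

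**The concern.** Stratified blocks force the arms to be nearly balanced on severity and centre. If those factors affect how fast virus clears, the treatment comparison varies less from trial to trial than it would under simple randomisation. A log-rank test that ignores the strata still uses a variance that includes the between-stratum variation. The variance is then too large, so the test rejects less often than its nominal level under the null and less often than it could under the alternative.

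The protocol names stratification for survival, a secondary endpoint, but not for the primary endpoint. At stake is some power in the one confirmatory test, in a trial planned at 80%.

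**Working it through.** **Inputs from the Statistics section.** "we estimated the mean time to clearance (natural log scale) of 2.17 days and standard deviation 0.74"; 240 patients and 80% power for a factor of 0.76; 120 patients and 80% power for a factor of 0.68. Alpha is not stated, so two-sided 5% is assumed.

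**Step 1: reproduce the stated power.** For a comparison of mean log times, power = Φ(|ln factor| / (SD·√(4/N)) − 1.96).

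- N = 240: |ln 0.76| = 0.2744; 0.74·√(4/240) = 0.0955; 0.2744/0.0955 = 2.87; Φ(0.91) = 81.9%.
- N = 120: |ln 0.68| = 0.3857; 0.74·√(4/120) = 0.1351; 0.3857/0.1351 = 2.85; Φ(0.89) = 81.4%.

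Both agree with the stated 80%. Stratification plays no part in this calculation.

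**Step 2: simulate the planned test with and without strata.** There were 6,000 trials per scenario, each with 240 patients, log-normal times, total log-SD held at 0.74, three centres by two severity groups (six cells), permuted blocks of 4 and 6 within cells, and no censoring. Power is at factor 0.76 and type I error at factor 1. Both tests were applied to the same simulated trials.

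Assumed, because the documents give no values: the severe share, the centre shares (60%, 25%, 15%), and the part of log-time variance explained by severity (R²) and by centre. With severe share p, the implied severe-to-mild ratio of clearance times is exp(0.74·√R²/√(p(1−p))). For p = 0.2 and R² = 0.10 this is exp(0.74·0.316/0.4) = 1.8.

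| Assumed scenario | Time ratio, severe v mild | Power, plain | Power, six strata | Type I, plain | Type I, six strata |
|---|---|---|---|---|---|
| Strata not prognostic | 1.0 | 74.0% | 73.6% | 5.0% | 5.2% |
| Severity 5%, 20% severe | 1.5 | 74.1% | 75.4% | 4.7% | 5.1% |
| Severity 5%, 5% severe | 2.1 | 73.8% | 75.9% | 4.9% | 5.1% |
| Severity 10%, 20% severe | 1.8 | 73.5% | 77.8% | 4.2% | 5.2% |
| Severity 20%, 20% severe | 2.3 | 73.4% | 82.1% | 3.2% | 5.6% |
| Severity 20%, 40% severe | 2.0 | 75.6% | 82.3% | 3.8% | 5.3% |
| Severity 10% + centre 10%, 20% severe | 1.8 | 75.6% | 82.6% | 3.2% | 5.3% |
| Severity 20% + centre 10%, 20% severe | 2.3 | 75.3% | 87.2% | 2.0% | 4.9% |

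Simulation standard errors are about √(0.74·0.26/6000) = 0.6 points for power and √(0.05·0.95/6000) = 0.3 points for type I error. The 5.6% entry is a little over two standard errors above 5%, so a small part of the gain in that row may reflect a slightly liberal stratified test.

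**Step 3: severity alone or severity and centre.** Where centre has no effect, stratifying by severity alone does as well (78.2% against 77.8% in the severity 10% row). Where centre explains a further 10%, severity alone gives 79.3% against 82.6% for all six cells.

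**Step 4: cross-check.** A second simulation (4,000 trials per scenario, times rounded to daily swab midpoints, 20–40% severe) compared the plain test with one stratified by severity. At a time ratio of 1.5, power was 73–76% plain and 75–78% stratified. At 2.0 it was 74–76% and 81–83%. With no severity effect it was 75% for both.

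**The case against.** The strongest objection is that silence is not a decision. The protocol never calls the primary test unstratified, and a journal article may leave the strata of a named test to the SAP. This stands in part: a reader might infer that the authors chose to leave the strata out, and the text does not show that. But the primary method is given in the protocol itself, and only the other secondary endpoints are expressly sent to the SAP. The SAP need only be finished before database lock. Interim reports after 60 and 120 participants, prepared by the study statistician, show time to clearance by arm. A choice of strata made after those looks would be open to question.

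Other stronger readings are tempting and are not supported:

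- **That power is lost as a matter of fact.** The documents give no figure for the effect of severity or centre on clearance. Large losses need a strong effect: with 20–40% severe, a ratio of 2.0 means severity explains p(1−p)·(ln 2)²/0.74² = 14–21% of all log-time variance.
- **That the omission is peculiar to the primary endpoint.** The survival model omits centre too, and the adverse event tests use no strata. The text shows uneven detail.
- **That the unstratified hazard ratio is biased.** It is closer to 1 when severity matters because it estimates a marginal effect; the stratified one is conditional on stratum.
- **That missing strata explain the gap between about 74% and the stated 80%.** They do not. With strata that have no effect, the plain log-rank test already has 74.0% power, because it is applied to log-normal times while the sample size matches a comparison of log means. That is a separate matter.

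**Conclusion.** The concern holds in conditional form. The primary analysis is stated without the factors used to stratify randomisation, while the survival model names one of them. If severity explains about 5%, 10% or 20% of log-time variance with 20% severe, the plain log-rank test gives up about 1 to 2, 4 and 9 points of power respectively. Prognostic centres would add to this. If the strata do not predict clearance, naming them costs under half a point, which is within simulation error.

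The matter is efficiency and clear specification. Type I error is not inflated, so a positive result from the plain test would remain valid. The sizes rest on the log-normal model with total SD 0.74, two-sided 5%, no censoring, and assumed severe shares, centre shares and variance shares. The direction does not depend on the particular values chosen, but the size does. The change is worth making because the possible gain is much larger than the possible cost.

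**What to change.** In Statistics (Statistical and analytical plans), state that the primary log-rank test and Cox model are stratified by disease severity as randomised and by recruiting centre, that small centres are pooled by a stated rule, and that the unstratified test is reported as a sensitivity analysis. Fix the pooling rule, including its numerical threshold, before any by-arm look at the data. The article reports two participants enrolled, so this can precede the interim analyses at 60 and 120. If a signed SAP already says this, a cross-reference is enough.

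The cost is one sentence and no new data or procedures. The downsides are a negligible loss of power if the strata are not prognostic, and a hazard ratio that is conditional on stratum and should be described as such.
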